## Abstract

Hemiplegic cerebral palsy (CP) is a subcategory of CP which is characterized by sensory motor deficits primarily on one side of the body that adversely affects functionality. Virtual reality (VR) systems have been advanced in the recent past for the use in rehabilitation of patients with neurological conditions. Virtual reality has an inherent motivational component that provides the much-needed compliance for active participation by children. The rationale of the proposed study is to investigate the effect of VR and haptic feedback for improvement of upper extremity function of children with hemiplegic cerebral palsy. This comparative experimental study will be recruiting 36 children with hemiplegic CP and will be treating them by VR and haptic feedback along with conventional physiotherapy in group A and by conventional physiotherapy only in group B. The children will undergo the treatment for six weeks (five days/week) with each session extending for 60 minutes/day. The primary outcome measures including `nine-hole peg test´ (9HPT) and `box and block test´ (BBT) will assess the manual dexterity and secondary outcome measures including `ABILHAND-kids´ and `WeeFIM (self-care)´ will assess the functional independence that are hypothesized to be gained by haptic enhanced VR intervention when combined with the conventional therapy.

## Introduction

**Background and rationale:** cerebral palsy (CP) in India has a prevalence of 2.95 per 1000 children (95% CI 2.03-3.88) [1]. Hemiplegic CP is a subcategory that accounts for a substantial number of all cases [2]. It is characterized by sensory motor deficits, primarily on one side of the body, that adversely affects functionality. Approximately 50% of children with hemiplegic CP have greater impairment in the upper extremity, particularly in the hand, as compared to the lower extremity [3]. Preferential hand usage of the non-paretic hand often results in the neglect of the paretic hand that adversely affect gross motor function classification system (GMFCS) and manual ability classification system (MACS) scores. Technologically advanced virtual reality (VR) systems have been used in the recent past in rehabilitation of patients with neurological conditions. Although numerous studies report promising results in adults with stroke [4,5], a limited number of studies have been undertaken that combine the use of VR and haptic feedback for children with infantile hemiplegia. Ravi *et al*. concluded that there is a need for research to establish the place of VR rehabilitation for children with CP [6]. Virtual reality has an inherent motivational component that provides the much-needed compliance for active participation by children. The inner drive to play VR based games that provide a real-world experience, is almost invariably present in school-aged children. This can be tapped for obtaining therapeutic benefits. Haptic feedback or force feedback enhances the fine-tuning of desired motor responses [7]. The use of paretic hand during the session may lead to the carry over for the functional tasks that can be gauged using appropriate outcome measures. The rationale of the proposed study is to investigate the effect of VR and haptic feedback for improvement of upper extremity function of children with hemiplegic cerebral palsy. The parents of children with infantile hemiplegia have a common primary concern of less or no functional use of paretic hand. Activities like reaching out, grasping, carrying and releasing by the affected upper limb are often inadequate. They need assistance in activities of daily living. Parents mention that children need repeated prompts for the use of paretic hand and that the children refrain from taking initiative to put the affected hand to function. This study aims to utilize the appeal in VR gaming systems and haptic feedback for bringing out the children´s inherent potential to use their paretic upper extremity and objectively record its effectiveness in improving function.

Virtual reality has an inherent motivational component that provides the much-needed compliance for active participation by children. The inner drive to play VR based games that provide a real-world experience, is almost invariably present in school-aged children. This can be tapped for obtaining therapeutic benefits. Haptic feedback or force feedback enhances the fine-tuning of desired motor responses [7]. The use of paretic hand during the session may lead to the carry over for the functional tasks that can be gauged using appropriate outcome measures. The rationale of the proposed study is to investigate the effect of VR and haptic feedback for improvement of upper extremity function of children with hemiplegic cerebral palsy. The parents of children with infantile hemiplegia have a common primary concern of less or no functional use of paretic hand. Activities like reaching out, grasping, carrying and releasing by the affected upper limb are often inadequate. They need assistance in activities of daily living. Parents mention that children need repeated prompts for the use of paretic hand and that the children refrain from taking initiative to put the affected hand to function. This study aims to utilize the appeal in VR gaming systems and haptic feedback for bringing out the children´s inherent potential to use their paretic upper extremity and objectively record its effectiveness in improving function.

**Objectives:** objectives of the study are to find the effectiveness and impact of VR and haptic feedback along with conventional physiotherapy (PT) for improving the upper extremity function, functional independence in children with hemiplegic cerebral palsy. Also, we will be evaluating the difference between improvement of upper extremity function by VR with haptic feedback along with conventional physiotherapy and by conventional physiotherapy only.

## Methods

The enrollment, intervention, and assessment of this study will be followed as recommended by standard protocol items recommendation for intervention trials (SPIRIT), 2013 as illustrated in Table 1 and Figure 1 [8].

**Table 1 T1:** schedule of enrolment, intervention and assessment where t1 is enrolment and pre-intervention assessment

	Study period			
	Enrolment	Allocation	Post-Allocation	
Timepoint	-t1	0	Intervention (t1-t10)	Post-test (t11)
**Enrolmen**t				
Eligibility screen	X			
Informed consent	X			
Allocation		X		
**Intervention**				
VR and haptic feedback + Conventional PT			X	
Conventional PT			X	
**Assessment**				
**Baseline variables**				
GMFCS, MACS	X			
**Outcome measures**				
9HPT, BBT, ABILHAND-Kids, WeeFIM (self-care)	X			X

t1-t10: duration of intervention; t11: post intervention assessment; VR: virtual reality; PT: physiotherapy; GMFCS: gross motor function classification system; MACS: manual ability classification system; 9HPT: nine hold peg test; BBT: box and blocks test; WeeFIM: functional independence measure for children

**Figure 1 F1:**
[figure not shown]
shows the study procedure in the form of a flow chart

**Study setting:** this trial will be conducted at Neurosciences Center, Department of Neurosurgery and Neurology, Neurorehabilitation Division of Acharya Vinoba Bhave Rural Hospital, Datta Meghe Institute of Medical Sciences, Sawangi (Meghe), Wardha, Maharashtra, India. The children referred for physiotherapy intervention at the Neurorehabilitation Division will be screened for eligibility criteria.

**Eligibility criteria:** the inclusion criteria will comprise school aged children between 6 and 12 years diagnosed with hemiplegic CP, mild or no difficulty understanding commands, ability to communicate age appropriately or with some difficulty (but a new listener can understand), no uncorrected vision, hearing without the need of a hearing aid, manual ability classification system (MACS) level I-III, gross motor function classification system (GMFCS) level I-III, and willingness to participate. However, the exclusion criteria will be mixed or other types of CP, cognitive impairment to an extent that defers understanding of commands, epilepsy, severe visual and/or auditory deficit, history of surgical procedures in last 6 months, history of botox treatment in last 3 months and enrollment in other clinical trials.

**Intervention:** the participants in the experimental group (group A) will undergo 30 minutes of conventional physiotherapy including activities for strengthening of weak muscles like wrist extensors and forearm supinators, stretching of tight muscles like wrist flexors and forearm pronators, weight-bearing activities like push-ups and quadripod position along with 30 minutes of VR and haptic feedback-based training of upper extremity by playing a serious game with real life-like experience and force feedback. Material for VR and haptic feedback intervention is shown in Figure 2. The participants in the control group (group B) will receive 60 minutes of conventional physiotherapy including activities for strengthening of weak muscles like wrist extensors and forearm supinators, stretching of tight muscles like wrist flexors and forearm pronators, weight-bearing activities like push-ups and quadripod position, along with reach, grasp, carry and release activities and fine motor activities for hand function training using pegboards. Post-intervention data will be collected for both groups using primary and secondary outcome measures.

**Figure 2 F2:**
[figure not shown]
material that will be used for providing virtual reality and haptic feedback-based intervention for participants in the experimental group, including television screen (1), playstation 4 that provides virtual reality-based gaming with haptic feedback enhanced hand controls (2), DVD of a game named Gran Turismo- the real driving simulator (3)

### Outcomes

**Primary outcome measures:** nine hole peg test (9HPT) will be used to evaluate fine motor function. Moderately high test-retest reliability and high interrater agreement was demonstrated by Smith *et al*. [9]. Correlations between the scores on the 9HPT and purdue pegboard test reveal sufficient concurrent validity of these measures, and a significant difference in test scores between regular and special education groups provided further indication of construct validity. Thus, 9HPT is an effective tool for estimating the fine motor dexterity of school-aged children [9]. The board with pegs for 9HPT is shown in Figure 3 box and blocks test (BBT) will be used as a test of unilateral gross manual dexterity. It is administered by asking the subject to one-by-one move, the maximum number of blocks from one compartment of a box to another of equal size, within 60 seconds. The test showed very high inter-rater, test-retest reliability and excellent construct validity [10] BBT kit is shown in Figure 4.

**Figure 3 F3:**
[figure not shown]
shows nine pegs with nine-hole peg board that will be used for 9HPT

**Figure 4 F4:**
[figure not shown]
shows 150 blocks with a partitioned box that will be used for BBT

**Secondary outcome measures:** ABILHAND-Kids will be used to evaluate upper extremity function. It is a 21-item functional ordinal scale specifically developed to measure manual ability in children with CP. Its measurement precision is considered highly adequate for clinical practice. Parents are requested to fill the questionnaire on the basis of their perception of the level of difficulty that a child faces during the performance of each activity in the list on a three-tier scale of `impossible´, `difficult´, `easy´ [11]. The linear measures obtained by the Rasch model can be used to make a comparison quantitatively regarding the manual ability of children with CP [12]. The test has shown excellent test-retest reliability as well as internal consistency [11]. It has excellent convergent validity with MACS [13]. WeeFIM (self-care section) will be used for evaluating functional independence. Functional independence measure for children is also known as WeeFIM. It can be used to estimate the `burden of care´ for children with developmental disabilities between 6 months to 21 years of age [14]. The performance of task is categorized as `dependent´ if the score is between 1-5 and is categorized as `independent´ if the score is 6 or 7. Score 1 indicates total assistance, score 2 indicates maximal assistance, score 3 indicates moderate assistance, 4 indicates minimal assistance, score 5 indicates supervision or set-up, score 6 indicates modified independence that includes an assistive device usage or not completing the task in a timely or safe manner and score 7 indicates complete independence i.e. the child completes the task without using a device [14]. The test-retest reliability is excellent for children with disabilities [15].

**Sample size:** sample size of 36 was calculated with 90% of confidence interval considering the dropouts, with 18 participants in each group by using G*Power software. A convenient sampling technique will be used.

**Recruitment and allocation:** potential participants will be screened for eligibility criteria and after obtaining well-informed written consent of the parent(s) or legal guardian, the child will be recruited as a participant. The participants will be distributed in 1: 1 manner into experimental group/group A (VR and haptic feedback in addition to the conventional physiotherapy) and control group/group B (conventional physiotherapy only).

**Data collection:** pre-intervention data will be collected using predetermined primary and secondary outcome measures. The training would be carried out for 6 weeks (5 days a week). The duration of each session would be 60 minutes. Virtual reality and the haptic feedback with conventional physiotherapy, and conventional physiotherapy alone are independent variables. Upper extremity function and functional independence are dependent variables. Data collected will be noted down and will be placed in a tabular format.

**Statistical methods:** after consultation with the statistician, statistical analysis will be done by using descriptive and inferential statistics using t-test, Wilcoxon signed-rank test and Mann-Whitney U test. Software SPSS 27.0 version and GraphPad prism 7.0 version will be used in the analysis. The changes in the outcome measures brought about after the course of 6 weeks of intervention will be analyzed by mixed-effects linear models across `time´ (pre-intervention vs post-intervention) and `group´ (experimental vs control). The age of participants and baseline scores of outcome measures between the two groups will be compared using t-tests. A p-value of less than 0.05 will be considered as level of significance. If subjects are lost to follow-up, an intention-to-treat analysis will be carried out. The results will be interpreted to note any significant statistical and/or clinical differences. The results will be accounted and documented as per the CONSORT guidelines.

**Trial design:** this is an interventional, non-randomized, active controlled, superiority trial with allocation ratio of 1: 1 in experimental group and control group.

**Ethics approval:** the research study was ethically approved by the Institutional Ethics Committee, Datta Meghe Institute of Medical Sciences on 29^th^ January 2021 with reference number DMIMS (DU)/IEC/2020-21/131. The Doctoral Research Committee approved it on 9^th^ April, 2021. The research protocol was submitted to Clinical Trials Registry of India on 16^th^ November, 2021 with reference number REF/2021/11/048970. The trial was registered in Clinical Trials Registry of India (CTRI) on 23^rd^ December 2021 with the registration number CTRI/2021/12/038861.

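### Baseline t-tests with 18 children per group cannot establish comparability in a non-randomised trial, and the stated model does not adjust for age or MACS as predictors of change

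*Protocol article*

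**What the plan says.** Under Trial design, the protocol article states: "this is an interventional, non-randomized, active controlled, superiority trial". The Sample size paragraph gives 18 children per group and adds: "A convenient sampling technique will be used". Recruitment and allocation describes a 1:1 split, with no matching or stratification.

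Two sentences under Statistical methods bear on comparability:

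- The baseline check: "The age of participants and baseline scores of outcome measures between the two groups will be compared using t-tests". The article does not say what follows from a significant or a non-significant result.
- The outcome analysis: changes over the six weeks are to be examined with "mixed-effects linear models across `time´ (pre-intervention vs post-intervention) and `group´ (experimental vs control"). No other model term is named.

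Table 1 lists GMFCS and MACS as baseline variables taken at enrolment. Neither appears in the list of baseline tests or among the model terms. Eligibility admits "school aged children between 6 and 12 years diagnosed with hemiplegic CP", with MACS and GMFCS levels I to III.

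**The concern.** Without randomisation, nothing in the design makes the groups alike in expectation, so measured confounding has to be dealt with in the analysis. The article answers this with significance tests that lead nowhere. With few children, a non-significant result is weak evidence of balance, and a significant one triggers no correction.

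The admitted range of age and manual ability is wide for a trial of this size. If older children, or children at a particular MACS level, improve faster or slower over six weeks and are unevenly split between the groups, the difference in change mixes that pattern with the treatment effect. The variables needed to address this are already being collected.

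**Working it through.** **Inputs.** From the article: 18 per group (Sample size); significance at p below 0.05 (Statistical methods; two-sided assumed, since sidedness is not stated); ages 6 to 12 (Eligibility criteria). Not in the article, so assumed: the size of a relevant imbalance (0.2 to 1.0 SD), the correlation of a covariate with change (0 to 0.5), and the age SD (uniform over 6 to 12, giving 6/√12 = 1.73 years). There is no figure of the plan's own to reproduce on this point.

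**Step 1: what the baseline t-test can detect.** Degrees of freedom are 18 + 18 − 2 = 34 and the critical value is 2.032. The non-centrality for a true imbalance of d SD is d × √(18/2) = 3d. Exact noncentral-t results:

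| True imbalance (SD) | Power | Missed |
|---|---|---|
| 0.2 | 9% | 91% |
| 0.3 | 14% | 86% |
| 0.5 | 31% | 69% |
| 0.8 | 65% | 35% |
| 1.0 | 83% | 17% |

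Power reaches 50% at 0.67 SD and 80% at 0.96 SD. The observed difference needed for significance is 2.032 × √(2/18) = 0.68 SD, or 0.68 × 1.73 ≈ 1.2 years of age under the uniform assumption.

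**Step 2: what the stated model already removes.** If a covariate shifts a child's score by the same amount at both visits, the shift cancels in post minus pre. In simulation with a 0.5 SD age imbalance and age correlated 0.45 with the score at both visits, a post-only comparison is biased by 0.5 × 0.45 ≈ 0.22 SD, but the change contrast by 0.00.

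**Step 3: what it does not remove.** If the covariate correlates r with change, the bias in the change contrast is d × r, in SD units of change:

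- r = 0: 0.5 × 0 = 0
- r = 0.3: 0.5 × 0.3 = 0.15
- r = 0.5: 0.5 × 0.5 = 0.25

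A simulation of 40,000 trials with no treatment effect agrees. At d = 0.5 and r = 0.3 to 0.5, the unadjusted bias is 0.15 to 0.25 SD and the type I error 0.072 to 0.113. Adjusting for the covariate brings bias to about 0 and type I error to 0.049 to 0.051. In the 69% of trials where the baseline test was non-significant, a bias of 0.10 to 0.17 SD remained.

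Regression to the mean adds a second route. If the groups differ on an outcome's own baseline score and part of that difference is transient, the gap narrows by the second visit without any treatment effect. The article gives no pre-post correlation, so this part is not sized.

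**Step 4: which adjustment has an effect.** With complete pre and post data, adding age as a main effect to a random-intercept model leaves the group-by-time estimate unchanged, because a main effect acts equally at both visits. In a simulated dataset the estimate was identical with and without it, and moved only when an age-by-time term was added.

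**The case against.** The strongest reply is that the plan does more than run baseline tests. It analyses change, and that contrast removes constant level differences, including those due to age or MACS. This stands. A reader might infer that wide differences in dexterity between children bias the comparison by themselves, or that a 0.45 correlation of age with the score produces a 0.22 SD bias. The stated analysis does not support that: Step 2 gives zero, and the 0.22 SD belongs to a post-only comparison.

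A reader might also infer that adjustment is worth 20 to 26 children per group, from 18/(1 − R²) with R² of 0.1 to 0.3 (20.0, 22.5, 25.7). Those R² values are assumptions, and the formula ignores the variance cost of estimating the covariates. With two covariates and that cost included, the equivalents are about 19, 21 and 24 when the covariates are balanced. They are about 17, 19 and 21 when both are imbalanced by 0.5 SD, so weakly predictive covariates can lose precision. The case for adjustment is bias, not precision.

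The article never says that a non-significant test will be read as proof of balance, and its descriptive statistics may well include MACS and GMFCS. Nor does the test miss everything: at 0.8 SD it detects 65%, and the article sets no threshold for a relevant imbalance.

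Finally, this is a condensed article and a fuller analysis plan could name covariates. That is fair as far as omission goes. But the article itself states both the comparability check and the model terms, and the point is directed at those.

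**Conclusion.** The point holds, within limits. In a non-randomised trial of this size the stated t-tests cannot establish comparability: the miss rate is 69% at 0.5 SD and above one half for any imbalance below about 0.67 SD. The stated model protects against constant level differences. It does not protect against measured predictors of change, or against regression to the mean. The bias from a predictor of change is 0 if age and MACS are unrelated to change, and about 0.15 to 0.25 SD for a 0.5 SD imbalance with a correlation of 0.3 to 0.5. Both the imbalance and the correlations are assumptions, since the article gives neither. The power figures rest only on 18 per group, a two-sided 5% level and the usual t-test assumptions; dropout would lower them (74% missed at 0.5 SD with 15 per group). This weakens the main group comparison and should be corrected, but does not invalidate the trial.

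**What to change.** - Drop the baseline t-tests. Tabulate age, MACS, GMFCS and the baseline score of each outcome by group, with standardised differences.
- For every outcome, prespecify one of two adjusted analyses, whatever imbalance is seen: (a) an ANCOVA of the post-intervention score on group, that outcome's own baseline score, age and MACS; or (b) the mixed model with age-by-time and MACS-by-time terms. Main effects of age and MACS alone would not change the result. Only (a) conditions on the outcome's own baseline and so addresses regression to the mean directly. The two rest on different assumptions, so the choice should be made before data are seen.
- State as a limitation that adjustment deals only with measured variables and that unmeasured selection into the groups remains.

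The cost is a change of wording and no new data: about two further degrees of freedom out of 36 children, and some loss of precision if the covariates turn out imbalanced but weakly predictive.

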On the other hand, the VR-based rehabilitation is designed to offer therapy is characterized by repetitive task-specific movements that include abduction and opposition of the thumb, which is often difficult for children with hemiplegic CP on the affected side. Haptic feedback finely tunes the motor response within a virtual environment, and the children are expected to look forward for such enjoyable sessions to tap their high neuroblastic potential. Play station is a motivational training tool for children with CP and has the potential to improve UE function [20]. The primary outcome measures will assess the manual dexterity (9HPT and BBT) and secondary outcome measures (ABILHAND-Kids and WeeFIM) will assess the functional independence that are hypothesized to be gained by haptic enhanced VR intervention when combined with the conventional therapy. The advantages of the haptic enhanced VR study include the customized approach towards the rehabilitation protocol and the responsiveness of the VR system during the intervention. To avoid any disparity between the two groups, the total rehabilitation time will be the same for both groups. The results of the study will aid the children with unilateral CP in the future by providing a fun way of utilizing the advanced technology of rehabilitation.

**Limitations:** this study will not focus on participation of the child in the society in context of International Classification of Functioning, Disability, and Health (ICF). Long term follow up to observe maintenance or regression of the possible effects will not be carried out. Investigator is not blinded.

**Probable implications:** motor learning principles are well knit in context of VR along with force/tactile feedback that would help the children in learning skills related to manual dexterity. If the children show improvement in their hand function, burden of care on the caregivers will decrease as the child will become independent in activities of daily living. The study may pave the way for further advancement of technology for the use in younger children with infantile hemiplegia for early intervention.

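### Two unranked primary outcomes share one p<0.05 threshold, and no rule says whether one or both must be significant to claim superiority

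*Protocol article*

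**What the plan says.** Under Outcomes, the protocol article lists two primary measures and gives each its own construct. The first: "nine hole peg test (9HPT) will be used to evaluate fine motor function". The second, BBT, "will be used as a test of unilateral gross manual dexterity". The Discussion groups them under one heading: "The primary outcome measures will assess the manual dexterity (9HPT and BBT"). No section puts one ahead of the other or combines them into a single score.

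Statistical methods set one threshold for the whole analysis: "A p-value of less than 0.05 will be considered as level of significance". They name several procedures ("inferential statistics using t-test, Wilcoxon signed-rank test and Mann-Whitney U test") and state that the changes over six weeks "will be analyzed by mixed-effects linear models across" time and group. None of these is tied to a particular primary outcome or to a success criterion. The section then says: "The results will be interpreted to note any significant statistical and/or clinical differences".

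Trial design states: "this is an interventional, non-randomized, active controlled, superiority trial with allocation ratio of 1: 1". ABILHAND-Kids and WeeFIM (self-care) are labelled secondary.

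**The concern.** A superiority trial needs a rule for when superiority has been shown. With two primary outcomes, the rule must cover the case where one is significant and the other is not. The article leaves that case open, while it fixes a flat 0.05 and an interpretation sentence that looks for *any* significant difference. Read together, these most naturally allow a claim on either outcome at an unadjusted level, and the stated 5% is then not the error rate of the primary claim.

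The gap matters more because the investigator is not blinded, as the Limitations say. If the rule is chosen after the results are seen, a split result can be presented as a success or a failure at will.

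**Working it through.** **Inputs from the article.** Two primary outcomes; threshold 0.05 for each; 18 participants per group (36 in total, said to allow for dropouts).

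**Inputs the article does not give, taken as assumptions.** Two-sided tests; one between-group test per outcome; correlation ρ between the two test statistics from 0 to 0.9; no true effect on either outcome (the global null).

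**Step 1. One test.** A single two-sided test at 0.05 has a 5% chance of a false significant difference, of which 2.5% lies in the direction of benefit. This is the only situation in which the stated threshold equals the error rate of the claim without a further rule.

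**Step 2. Either outcome suffices, difference in either direction.** Familywise error = 1 − P(|Z1| < 1.96 and |Z2| < 1.96).
- Independent outcomes: 1 − 0.95² = 0.0975.
- Correlated outcomes, from the bivariate normal distribution, are in the table.

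**Step 3. Either outcome suffices, benefit only.** Error = 1 − P(Z1 < 1.96 and Z2 < 1.96). Independent outcomes: 1 − 0.975² = 0.0494.

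**Step 4. Both outcomes required.** The chance that both are falsely significant is 0.05 + 0.05 minus the Step 2 figure. Independent outcomes: 0.10 − 0.0975 = 0.0025. If one outcome has a real effect and the other has none, the error of a joint claim is still at most 5%.

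**Step 5. Holm.** Under the global null, any rejection needs the smaller p-value to be below 0.025. Independent outcomes: 1 − 0.975² = 0.0494.

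| Assumed ρ | Either suffices, two-sided | Either suffices, benefit only | Both significant | Holm |
|---|---|---|---|---|
| 0 | 9.75% | 4.94% | 0.25% | 4.94% |
| 0.5 | 9.07% | 4.54% | 0.93% | 4.65% |
| 0.7 | 8.35% | 4.17% | 1.65% | 4.30% |
| 0.9 | 7.04% | 3.52% | 2.96% | 3.62% |

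Over ρ = 0.5 to 0.9 the two-sided figure is 9.07/5 = 1.8 to 7.04/5 = 1.4 times the nominal level.

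**Step 6. Cost in detectable effect.** The sample size of 36 cannot be reproduced, because the article gives no effect size, SD, power or dropout rate. What can be computed is the standardized difference that a two-sample t-test (noncentral t) detects with 80% power:
- 18 analysed per group: 0.961 SD at 0.05 and 1.067 SD at 0.025.
- 16 analysed per group, as an example of dropout: 1.024 SD and 1.138 SD.

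**The case against.** The strongest reply is that the article never says one positive outcome is enough. The sentence about noting differences is a general remark on interpretation and mentions neither primary outcomes nor superiority. The Discussion presents the two tests jointly as measures of manual dexterity, which also fits a plan to require both, and then the error stays at or below 5% with no adjustment. This stands: the either-one rule is an inference, and the figures in Step 2 are conditional on it.

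A second reply is that a journal article condenses the full protocol, and that alpha allocation may be settled in that protocol or in an SAP, neither of which is shown. This lowers the severity but does not dispose of the point. The article itself commits to the flat 0.05 and to the search for any difference, and an adjusted rule elsewhere would depart from that published text.

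Three stronger readings are tempting and are not supported:
- A reader might infer that the chance of a false claim of *benefit* is close to 10%. With two-sided tests it is at most 4.94%. It would reach 9.75% only with one-sided tests at 0.05, and the article does not state sidedness.
- A reader might take 9.75% as the expected error. It is the ceiling, and it needs independent outcomes. Two tests of manual dexterity in the same children are likely to be correlated.
- A reader might count all four outcomes as routes to success. The article labels ABILHAND-Kids and WeeFIM secondary, and nothing lets them carry the superiority claim.

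**Conclusion.** The point holds in a limited form. The article fixes two unranked primary outcomes and one unadjusted threshold, and gives no rule for combining them, so its text does not hold the error of the primary claim at 5%. If either outcome suffices, the tests are two-sided and neither outcome is truly affected, the familywise error is at most 9.75%, and about 9.1% to 7.0% at an assumed correlation of 0.5 to 0.9. The benefit-only error at most roughly doubles, from 2.5% to 4.94%. If both outcomes are required, there is no inflation and only the statement of the rule is missing.

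Severity is moderate. Allocation is non-randomized and the investigator is unblinded, so differences between the groups can arise from confounding or assessment bias, and no adjustment of alpha would remove them. The 5% that a corrected rule secures is the sampling error of the tests, not the full chance of a wrong conclusion.

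**What to change.** Add one sentence to Statistical methods. A suitable form: superiority is claimed under Holm across 9HPT and BBT, with the smaller of the two p-values tested at 0.025 and, if it passes, the other at 0.05. State there that the tests are two-sided, and that ABILHAND-Kids and WeeFIM are supportive and cannot carry the claim.

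Two alternatives also close the gap:
- **Require both primaries at 0.05.** No alpha adjustment is needed. The cost is power: if each outcome had 80% power and the two were independent, the chance of success would be 0.80 × 0.80 = 64%, rising towards 80% as the correlation rises.
- **Name one outcome as primary and test it at 0.05.** That outcome loses no alpha; the other becomes secondary.

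The cost of Holm is that the effect detectable with 80% power at the first step rises from about 0.96 to 1.07 SD with 18 analysed per group. This is a complete-data t-test approximation; the planned mixed model and any dropout would change the exact values. The rule should be fixed before outcome data are examined.
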